### Blinding

Because of the nature of the study, it will be clear to most participants whether they are allocated to the VR intervention or the control group. Thus, it is not possible to blind either the participants or the rehabilitation team, but they will be asked not to disclose any details about the allocation or the content of the VR. The two independent research assistants will be trained to administer the assessments and will be blinded to the allocation when entering data into the database. The researchers and the statistician performing the data analysis are blind to the treatment arm in which the participants are allocated. The rehabilitation team and the research assistant will only be involved in the data collection and will therefore not participate in the data analyses.

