### A description of the manual-based VR interventions

This manual-based VR study comprises the following three phases:Initial assessment: Within two weeks after the referral to the study, each patient will meet with the case manager in the municipality (brain injury coordinator). Here, a more thorough interview will ensure that the inclusion criteria are met and, in addition, asses the patient’s readiness for VR. Moreover, the participant will be fully informed about the content of the study, how participation is voluntary, and how they are free to withdraw at any time during the study. If written informed consent is obtained, each patient is assigned a unique trial ID number and baseline questionnaires will be filled out together with the following socio-demographic, employment, and clinical data: gender; date of birth; residence; civil status; nationality; income; pre-injury employment and education status; pre-injury occupation status; length of education; time since the brain injury; type and location of the brain injury; number of days hospitalized; the date of discharge; clinical diagnoses or any relevant medical events; and alcohol consumption or abuse. Participants will then be randomly assigned to either the VR intervention or the conventional VR. At last, each patient included in the VR intervention group will be asked to choose at least two family members to participate in the family intervention and one family caregiver which will participate actively in the individual sessions and serve as future support and resource facilitator to assist them in returning to work. This initial assessment will take approximately 50 min and the patient will have the opportunity to ask questions throughout the entire assessment. To exclude recruitment bias, patients that meet the eligibility criteria but refuse to participate in the study will be asked a few questions about their refusal. Hereafter, the patient will be contacted by external testers and baseline testing will be completed.The VR intervention program: The VR intervention lasts for a total of 6–9 months and consists of, first, six different modules (approximately three months) that are individually planned based on the patient needs and goals and, second, a work placement program (approximately 3–6 months). To ensure a uniform procedure of each of the different modules, comprehensive “standard operating procedures” (SOPs) will be developed by the rehabilitation team at the Brain Injury Centre before the beginning of the VR intervention. All members of the rehabilitation team (which includes six neuropsychologists, eight occupational therapists, and four physiotherapists) are already experienced in the VR intervention program and exceedingly specialized in ABI rehabilitation. They will go through a one-day workshop to be thoroughly introduced to the specific study protocol and the SOPs as recommended by Holmes et al. [31]. The six modules will be grouped into: (1) individual therapies, which includes neuropsychological sessions (10 h), balance between work and everyday life (20 h), and job matching (10 h); (2) grouped-based therapies, which includes psycho education (18 h), mindfulness (15 h), and physiotherapy training (15 h); (c) a manualized family intervention program (eight sessions of 90 min) [32] and an individual caregiver coaching, supporting the caregiver in assisting the patient using the different strategies and tools learned in the intervention in everyday life and at the workplace (12 h); (4) an individual work placement program including work practice (3–6 months), supported employment where the rehabilitation team is at the work place (30 h), and the development of a post-rehabilitation plan (4 h). The modules are planned based on the participant’s needs and goals thus, the length, duration, structure, and composition of the program will vary from patient to patient. The individual sessions and group sessions are delivered either in parallel or in serial depending on the patient.Group sessions will take place at the Brain Injury Centre BOMI and the individual sessions will most often take place in the patient’s home. The individual work placement intervention will take place at relevant workplaces, the patient’s current workplace, or at a new workplace found by the municipality or the Brain Injury Centre BOMI, depending on the individual case.Post-trial evaluation: An evaluation of the VR intervention will be performed by a self-developed semi-structured interview of each patient. Here, questions related to the recruitment procedure, the modules of the study, the timing of modules, and the coaching by the rehabilitation team will be collected. Furthermore, all case managers at the municipalities that referred participants to the study will be asked about their experiences and level of satisfaction.

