### Data collection and management

Data will be stored in a secure password-protected electronic database hosted by the Brain Injury Centre BOMI following Danish legislation. Over a period of three years, 84 individuals with ABI will be included in the study and assigned a unique trial ID number. Data will be collected prior to the intervention (baseline), at the end of the intervention, and at the six-month follow-up by various questionnaires (Fig. 1 and Table 1). All assessments will take place at the local rehabilitation center and will be done by two to three research assistants blinded to the intervention. Each assistant will receive thorough training in the assessment and will continue to be supervised throughout the study period. Data will be entered directly into a survey and exported into the database to ensure quality of the data. Access to data is restricted to the principle investigator and authorized researchers reported to the Danish Data Protection Agency. Furthermore, the data will be published in peer-reviewed scientific journals and the results will also be presented at national and international conferences.

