### Statistical analysis

Data analysis will be conducted using the statistical program R version 3.2.2. Baseline characteristics of the participants will be reported to ensure homogeneity between the VR intervention and the control group (reported as mean and standard deviation for continuous variables and proportions for categorical variables). Differences between baseline characteristics for continuous variables will be tested by an independent samples *t*-test or a Mann–Whitney U test dependent on the distribution of the data. Categorical variables will be analyzed by a Chi-square test. If any significant differences between the VR intervention and the control group are found, these will be adjusted for in the downstream analyses.

The differences between the VR intervention and the control group for the primary and secondary outcomes will be analyzed using repeated measurements statistical tools and multilevel analysis, including possible confounders (e.g. age, gender, ABI severity, socioeconomic status pre-injury, education, or recruitment site). *P* values and 95% confidence intervals will be provided and *P* < 0.05 will be considered statistical significant.

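### Baseline testing by the external testers follows random assignment, so the performance-test baselines are post-randomization measures taken when most patients know their arm

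*Protocol article*

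**What the plan says.** The order of events is in the Protocol article, section on the manual-based VR interventions, under the initial assessment.

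- After consent, "each patient is assigned a unique trial ID number and baseline questionnaires will be filled out together with the following socio-demographic, employment, and clinical data".
- Next: "Participants will then be randomly assigned to either the VR intervention or the conventional VR".
- Patients in the VR arm then choose their family members and caregiver. A sentence on patients who decline the study follows.
- Last: "Hereafter, the patient will be contacted by external testers and baseline testing will be completed".

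Other sections bear on this order:

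- Blinding: "it will be clear to most participants whether they are allocated to the VR intervention or the control group". Participants and the rehabilitation team are asked not to disclose the allocation.
- Data collection and management: "Data will be collected prior to the intervention (baseline), at the end of the intervention, and at the six-month follow-up by various questionnaires". It also says that assessments "will be done by two to three research assistants blinded to the intervention".
- Statistical analysis, on the baseline comparison: "If any significant differences between the VR intervention and the control group are found, these will be adjusted for in the downstream analyses". Outcomes are then analyzed with repeated-measurements and multilevel methods.

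**The concern.** A baseline value is safe to compare between arms, or to adjust for, because the allocation cannot have influenced it. A test taken after the patient has learned the arm loses that protection. Several Table 1 tests depend on effort: the dual-task Timed Up and Go, PASAT, the Wechsler subtest, Trail Making and the continuous performance test. A patient disappointed by usual care, or encouraged by a place in the specialized program, may perform differently.

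Two consequences follow. First, any such difference at baseline would be read as chance imbalance, and the analysis would adjust for it or measure change from it. Second, a patient who knows the arm can reveal it to the tester at the first visit. If testing came before assignment, there would be nothing to reveal.

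**Working it through.** **1. Order of the steps.** Set in sequence, the text gives: consent and trial ID; questionnaires with socio-demographic, employment and clinical data; random assignment; choice of family members in the VR arm; contact by external testers; baseline testing. The sentence on decliners stands just before the testing sentence, but decliners are not tested. The testing sentence can therefore only refer to enrolled patients whose initial assessment, including assignment, is over. No other section gives a different order.

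**2. Which measures are affected.**

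| Measure | Timing relative to assignment | Basis |
|---|---|---|
| Patient baseline questionnaires | before | stated in the initial assessment |
| Socio-demographic, employment and clinical data | before | stated in the initial assessment |
| Weekly hours at work or study (primary) | probably before | eligibility caps current hours at 15 per week, so they must be known at screening; Table 1 takes the outcome from a register or interview |
| Tests given by the external testers | after | stated in the initial assessment |

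The article does not list the instruments that make up the baseline testing. That they are the performance tests in Table 1 is a presumption, made because those tests need someone to administer them.

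**3. Possible size.** The plan gives no figure for this point, so there is none to reproduce. The following is an illustration on assumed values. Let s be the shift in one arm's baseline score caused by knowing the arm, in SD units, and let r be the baseline–follow-up correlation, with equal SDs. Let f be the fraction of s still present at follow-up. Relative to a comparison free of this effort effect:

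- baseline-adjusted analysis: bias = f·s − r·s = (f − r)·s
- change-score contrast: bias = f·s − s = (f − 1)·s

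If the shift is present at baseline and absent at follow-up (f = 0), the sizes are r·s and s:

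| | s = 0.1 | s = 0.2 | s = 0.3 |
|---|---|---|---|
| adjusted, r = 0.3 | 0.03 | 0.06 | 0.09 |
| adjusted, r = 0.5 | 0.05 | 0.10 | 0.15 |
| adjusted, r = 0.7 | 0.07 | 0.14 | 0.21 |
| change score | 0.10 | 0.20 | 0.30 |

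If the shift persists in full (f = 1), the change-score bias is (1 − 1)·s = 0. The adjusted estimate then carries (1 − r)·s, which comes from unblinded follow-up and not from the order at baseline alone.

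The sign depends on which arm shifts and in which direction, and the document settles neither. Trail Making is scheduled at baseline only, so no change score exists for it; it could enter only as a baseline comparison or a covariate.

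**The case against.** The strongest reply is that the damage is narrow. Patient questionnaires and employment data are collected before assignment, the primary outcome is not an effort test, and what remains is a handful of secondary measures. That stands, and it sets the weight of the point.

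It can also be said that disclosure is already addressed, since participants are asked not to reveal their arm and assessors are described as blinded. This stands in part. The request reduces the risk at the baseline visit without removing it, whereas testing before assignment would remove it there. The same risk exists at the end-of-intervention and six-month visits, and the reordering does nothing for those.

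The flow chart and the schedule figure are not available in the text reviewed and may make the order clearer. The written order is nevertheless plain.

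Four stronger readings are tempting:

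- A reader might infer that the baseline is no longer pre-treatment. The section on data collection places baseline before the intervention; what is lost is that these tests precede randomization.
- A reader might infer that all baseline values are compromised. The stated order contradicts this for patient questionnaires and employment data. For caregiver questionnaires the timing is not stated; VR patients choose their caregivers after assignment, so this is worth clarifying but is not established.
- A reader might infer that patients will be lost between assignment and testing and so drop out of the analysis. That is possible, but the article gives no rate and does not say that untested patients are excluded.
- A reader might take the tabulated biases as expected values. They are not: r, s and f are all assumed, and the article commits to neither a baseline-adjusted nor a change-score analysis.

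**Conclusion.** The point holds in a limited form. As written, the baselines taken by the external testers are post-randomization measures from patients who mostly know their arm, and the planned handling of baseline differences would treat any effect of that knowledge as chance. The problem lies mainly with the secondary performance outcomes and with tester blinding at the baseline visit.

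The size is unknown. The illustrative range of 0.03 to 0.21 SD (adjusted) or 0.1 to 0.3 SD (change score) rests on assumed r and s and on the shift being absent at follow-up. The conclusion also assumes that the baseline testing consists of the performance tests in Table 1. This is an inexpensive improvement to the design and does not threaten the primary comparison.

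**What to change.** In the initial-assessment paragraph, move the external testing forward so that the order is consent, confirmation of eligibility, baseline questionnaires, all tester-administered baseline tests, then assignment. State that no patient is assigned, and no allocation released, until the baseline record is complete. State also which Table 1 instruments the testers administer and when the caregiver questionnaires are completed.

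For any patient already tested after assignment, label those values as post-randomization measures, do not adjust for them as chance imbalances, and keep all randomized patients in the analysis.

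The sample size and alpha do not change. The cost is that assignment waits for the test appointment; the document does not give that interval. One limit remains: the Randomization section alternates arms within a municipality after the first patient, so the next arm can be predicted and withholding it does not fully conceal it. That is a separate issue, best settled in the same amendment.

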
### The conventional VR provided by the municipalities (usual care)

Individuals allocated to the control group will receive the conventional VR program provided by the municipalities over the same period of time. Thus, the participants in the control group will receive VR support by the local municipal authority that may vary in content and intensity. As for the intervention group, each individual in the control group will select a family caregiver that will go through the same questionnaires as the caregivers in the VR intervention group regarding HRQoL and functional level.

Furthermore, the case manager at the municipalities is obliged to: (1) refer patients to the study; (2) hand out the baseline questionnaires to the participants and their family caregivers; and (3) complete a questionnaire about each participant at the beginning and end of the study, and again at the six-month follow-up.

An evaluation of the conventional VR provided by the municipalities will be performed by the rehabilitation team using a self-developed semi-structured interview of each patient.

### Outcome measures

Primary and secondary outcomes are outlined in Table 1 and are measured at baseline, after the end of the intervention, and at the six-month follow-up. In addition, the family caregivers will be evaluated (Table 1).

**Table 1 Tab1:** Primary and secondary outcomes and outcomes related to family caregivers

Outcome	Assessment	Test tool	Assessment time:		
			Baseline	End	6-month FU
Primary outcome	Hours at work/study per week	Register-based or by interviews	**X**	**X**	**X**
Secondary outcomes	Proficiency on functional task	The Mayo-Portland Adaptability Inventory (MPAI-4) (participation index – rating will be done separately by the patient, relatives, and staff)	**X**	**X**	**X**
	Functional status	Glasgow Outcome Scale Extended (GOSE)	**X**	**X**	**X**
	Health-related quality of life	EuroQol Five Dimensions Questionnaire EQ-5D-3 L	**X**	**X**	**X**
	Anxiety and depression	Hospital Anxiety and Depression Scale (HADS)	**X**	**X**	**X**
	Fatigue	Dutch Multifactor Fatigue Scale (DMFS)	**X**	**X**	**X**
	Physical functioning	Timed Up and Go (dual task) (TUG)	**X**	**X**	**X**
	Self-perceived burden to others	Self-Perceived Burden Scale (SPB)	**X**	**X**	**X**
	Socio-demographic, employment, and clinical data	Structured interviews	**X**	**X**	**X**
	Working ability	Work Ability Index™ (version 2007)	**X**	**X**	**X**
	Assessment of intelligence	Wechsler Adult Intelligence Scale (subtest)	**X**	**X**	**X**
	Executive functioning	TRAIL Making Test A and B	**X**		
	Cognitive functioning	Paced Auditory Serial Addition Task (PASAT)	**X**	**X**	**X**
	Working memory	Connors Continuous Performance Test	**X**	**X**	**X**
Outcome family caregivers	Quality of life	EuroQol Five Dimensions Questionnaire EQ-5D-3L, SF-12	**X**	**X**	**X**
	The adaptability and cohesion dimensions in family interactions	Family Adaptability and Cohesion Scale (FACES-IV)	**X**	**X**	**X**
	Problem-solving ability	Problem Solving Inventory (PSI)	**X**	**X**	**X**
	Assess perceived burden among caregivers	Caregiver Burden Scale (CBS)	**X**	**X**	**X**
		Hospital Anxiety and Depression Scale	**X**	**X**	**X**

### Economic evaluation of the intervention

The economic consequences of the ABI will be evaluated using a two-stage approach. First, a budget impact analysis of the financial streams related to ABI for the two compared interventions will be performed to examine the affordability of the interventions. Second, the health gains will be quantified by the standardized questionnaire EQ-5D-3 L (health profiles and self-perceived health status). If relevant and feasible, a cost-utility analysis (quality adjusted life-years [QALYs]) from a societal perspective will be performed, including a cost-effectiveness acceptability curve to show the probability that the intervention will be cost-effective for a range of maximum prices that the municipalities will be willing to pay for an extra QALY.

Data on financial streams and costs are collected from the patients when discharged from hospital to the end of the follow-up period of the study by a self-developed questionnaire to the participating municipalities. Data collection will be based on routinely collected data, which can be retrieved from financial and administrative systems, in order to get an overall cost estimate on consumption of handicap compensating products and services (if the consumption of such services deviates significantly for the two types of interventions, i.e. marginal cost perspective). Non-priced usage of welfare services will be based on time usage and converted into monetary value by standard prices or local costs. Long-term effects on employment will be forecasted based on the observed employment effects during the follow-up period. Age-specific assumptions regarding employment will be set in order to calculate the averaged long-term effects.

In order to calculate the present value of the future gains of the interventions, a discount rate of 4% will be applied. Statistical uncertainty on the results will be calculated, in addition, to sensitivity analysis on critical assumptions (difference-in-difference analysis).

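### Costing one service category only if the arms differ significantly may shrink the incremental cost, and the societal label does not match a municipal cost source and threshold

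*Protocol article*

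**What the plan says.** All of this is in the protocol article, section Economic evaluation of the intervention, unless noted.

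- Two stages are planned: a budget impact analysis, then a cost-utility analysis if that proves relevant and feasible. The second stage "from a societal perspective will be performed", with an acceptability curve over the prices that municipalities would pay for an additional QALY.
- Cost data are obtained "by a self-developed questionnaire to the participating municipalities", drawing on routine financial and administrative systems.
- One category carries a condition. The plan seeks an "overall cost estimate on consumption of handicap compensating products and services", but only "if the consumption of such services deviates significantly for the two types of interventions". The gloss that follows is "i.e. marginal cost perspective". No test, threshold or direction is given.
- Other items carry no such condition: "Non-priced usage of welfare services will be based on time usage and converted into monetary value by standard prices or local costs". Employment effects are observed and then forecast.
- The section also says that statistical uncertainty will be calculated, with sensitivity analysis on critical assumptions.

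Elsewhere, Statistical analysis defines significance as P < 0.05, Sample size and power gives 42 patients per arm, and Trial design and hypotheses frames the economic question as whether the investment is sound for the municipalities.

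**The concern.** Two separate problems arise.

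First, whether a cost item enters the increment is decided from the trial's own data. The only definition of significance in the article is P < 0.05. Under that reading, a non-significant difference is replaced by exactly zero, while a significant one is kept at its observed and selectively large value. A trial sized for hours at work has no particular power for a service-use item, so absence of significance would say little about absence of a cost difference. The average effect is to pull the item's increment towards zero, whether the intervention raises or lowers use. A dropped item also has no variance in the total, so the acceptability curve treats its difference as known.

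Second, the declared perspective, the data source and the threshold do not agree. A societal analysis asks what all parties bear. The named instrument asks municipalities, and the threshold is a payer's. A reader comparing the cost per QALY with other societal analyses could be misled about what was measured.

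The stake is municipal investment, which the economic hypothesis addresses directly.

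**Working it through.** The economic section gives no cost difference, SD or power, so there is no planned figure to reproduce. The check asks what the rule does if it is applied as a test.

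**Inputs**
- n = 42 per arm (Sample size and power).
- Two-sided P < 0.05, critical value 1.96. The level is from Statistical analysis; two-sidedness is assumed.
- True difference d in SD units: assumed, because the documents give none. Range shown: 0 to 0.8.
- Also assumed: a normal approximation for the mean difference, and cost proportional to use.

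**Step 1: standard error.** SE = √(2/42) = 0.218 SD. An observed difference below 1.96 × 0.218 = 0.43 SD would be counted as zero.

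**Step 2: formulas.** Let Z ~ N(μ, 1) with μ = d × √(42/2) = d × √21.
- Chance of being counted: P = 1 − Φ(1.96 − μ) + Φ(−1.96 − μ).
- Expected counted value: E = μP + φ(1.96 − μ) − φ(−1.96 − μ).
- Expected counted share of the truth: E/μ.
- Overstatement when counted: E/(Pμ).

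**Step 3: worked case, d = 0.3.** μ = 0.3 × √21 = 1.375. P = 0.279 + 0.0004 = 0.280. E = 1.375 × 0.280 + 0.336 − 0.0015 = 0.719. Share = 0.719/1.375 = 0.52. Overstatement = 0.523/0.280 = 1.87, that is, about 0.56 SD shown for a true 0.3 SD. A simulation of one million draws with critical value 1.98 agrees: counted 27% of the time, mean 0.565 SD when counted, and average contribution 0.154 SD (0.154/0.3 = 0.51).

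**Step 4: range**

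| Assumed d (SD) | Counted | Expected share of truth | Overstatement when counted |
|---|---|---|---|
| 0 | 5% | no bias on average | – |
| 0.2 | 15% | 0.40 | 2.6 |
| 0.3 | 28% | 0.52 | 1.9 |
| 0.4 | 45% | 0.67 | 1.5 |
| 0.5 | 63% | 0.80 | 1.3 |
| 0.8 | 96% | 0.98 | 1.03 |

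Without the rule the expected share is 1.00 in every row.

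**Step 5: the other reading.** If the rule leaves out only costs known to be the same in both arms, the omitted difference is zero by construction and the increment is essentially unaffected.

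**Step 6: perspective, side by side.** No arithmetic applies.
- Label: societal.
- Named cost source: municipalities.
- Threshold: the municipalities' willingness to pay.
- Decision maker in the hypothesis: the municipalities.
- Element beyond municipal service cost: employment effects.

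Three of the four descriptors are municipal. Employment effects widen the scope but do not by themselves make the analysis societal.

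**The case against.** The strongest defence is the gloss itself. Marginal costing normally leaves out what does not differ between options, and the word for significant may mean material, not tested. That stands as a possible reading, so bias is conditional and not certain. It does not remove the problem: even a materiality rule has no stated criterion and would be judged after the data are seen. Costing the item in both arms gives the right increment under either reading.

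The loss also fades for large differences (expected share 0.98 at 0.8 SD). The cost-utility analysis is conditional and secondary, and the budget impact analysis makes no societal claim. The planned uncertainty calculation can describe only what is in the cost total, so it does not cover an item that has been removed.

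Four stronger inferences are tempting, and the documents do not support them.

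- *All service costs are conditional.* The condition attaches to one category; time-costed welfare services have none.
- *The costing is municipality-only.* Employment effects are considered, the outcome table takes hours from registers or interviews, and the sentence that data "are collected from the patients when discharged from hospital to the end of the follow-up period of the study by a self-developed questionnaire" is ambiguous about the patients' role.
- *Starting at hospital discharge biases the increment.* The text gives a collection window and does not say that costs before allocation enter the increment. Difference-in-difference, named with the sensitivity analyses, needs such data. Under sound randomisation, including these costs would add noise, with no expected difference between arms.
- *Family time is left uncounted.* The intervention includes "a manualized family intervention program" and caregiver coaching, but a condensed article need not list every cost item. Silence does not show omission, and nothing says whether family hours are recorded.

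**Conclusion.** The point holds in a limited form. For one cost category, an undefined significance condition may distort incremental cost. Applied as a two-sided P < 0.05 test at 42 per arm, it leaves on average about 40% to 80% of a true difference of 0.2 to 0.5 SD and drops that item's uncertainty whenever the test fails. These figures rest on assumed differences, the normal approximation and the testing reading. Under the common-cost reading there is little bias. The effect on total incremental cost cannot be sized, because the article does not give this category's share of cost.

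Independently of that, the societal label does not fit the named municipal cost source and the municipal threshold. This is an inconsistency within one section, in an analysis that may or may not be done. It is worth correcting because the results are meant to inform municipal spending.

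**What to change.** 1. Delete the significance condition. State that disability-compensation products and services will be costed in both arms for every patient, whatever the observed difference or P value.
2. Carry the item's uncertainty into the incremental cost and the acceptability curve, for example by bootstrapping patients within arm.
3. If some costs are to be left out as common to both arms, name them in advance and give the reason from the design, not from the observed data.
4. Relabel the cost-utility analysis as municipal (payer) perspective with employment effects. Alternatively, keep the societal label only if non-municipal costs are included, and name their sources.

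The first three changes cost slightly more data handling, because the item must be extracted for everyone. Relabelling costs a narrower claim; keeping the societal label costs additional data sources. The sample size and the clinical conduct of the trial are unaffected.
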